### Control variables

When testing changes in the mothers’ attentional disengagement, inhibitory control, and reflective functioning, we will control for the potential confounding roles of general maternal executive functions, and maternal psychopathology. As far as it concerns general executive functions, we will measure inhibitory control, working memory, cognitive flexibility, and planning through standardized neuropsychological tasks involving neutral stimuli. Specifically, we will use a go/no-go task [142], the Corsi Block-Tapping Task [143, 144], a short-form of the Berg Card Sorting Test [145–148], and the Tower of London Test [149–151]. All the tasks are computerized and retrieved from the open source software system PEBL - Psychology Experiment Building Language [152].

Concerning maternal psychopathology, we will administer the Symptom Checklist-90 Revised [153], a 90-item self-report questionnaire designed to evaluate the presence of psychopathology along different symptom dimensions and global distress indexes.

### Statistical analyses

Statistical analyses will be carried out according to intention-to-treat principles [154]. Data distributions will be inspected to check for normality and data transformation will be applied when normality assumptions are violated [155]. Missing data will be inspected to check whether they are missing completely at random, at random, or not at random, and multiple imputation procedures will be applied to manage them [156]. For the primary, the secondary, and the fourth aims, we will first adopt linear mixed models for intent-to-treat analyses and subsequently apply repeated measures models on complete cases. To estimate the intervention effect on parenting and on parental cognitive mechanisms, we will define experimental condition as between-subjects factor and time-point measurements as within-subjects factor. For our tertiary and fifth aims, we will use the Montoya and Hayes approach [157] in a repeated measures design to test whether changes in cognitive mechanisms mediate the intervention effects on parenting.

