### Quality of parenting in mothers with SUD

#### Observed parenting behaviors

Observed parenting behaviors constitute a key access to the quality of parenting in infancy and childhood, providing a measure of the parent’s ability to take care of the child and of the child’s actual experience of care [15–19]. Maternal SUD jeopardizes the quality of parenting behaviors, affecting in multiple ways sensitive parenting [15, 17, 20] and parental sensitive discipline [21, 22], two facets of positive parenting associated to favorable developmental outcomes in children [23, 24]. Compared to low-risk populations, mothers with SUD show less optimal sensitivity and responsiveness to children’s emotional signals [25–29] and are more inclined to be hostile, directive, and interfering with their activities [30–34]. These negative parenting behaviors have been linked to unfavorable outcomes in offspring, as insecure and disorganized attachments [35], and a higher risk to be involved with child protective services [36]. Moreover, mothers with SUD are more inclined to adopt negative disciplinary strategies [37], ranging from the use of harsh discipline [38–40] to the adoption of laissez-faire, characterized by withdrawal and lack of limit-setting, and role reversal [41, 42]. These practices tend to be ineffective and are related to several undesired developmental outcomes in children, including internalizing and externalizing problems [43, 44]. Therefore, parenting behaviors constitute one of the main targets of parenting interventions in the condition of SUD [45, 46]. In the present study, we aim to test the efficacy of the VIPP-SD, a short-term evidence-based parenting intervention based on attachment theory [17, 47] and social learning theory [48, 49], in improving positive parenting strategies in a clinical population of SUD mothers with young children. We will measure sensitive parenting and sensitive discipline using observational scales (the Emotional Availability Scales [50] and a scale for harsh discipline [51]) under various structured conditions (free-play and two compliance tasks), comparing mothers with SUD receiving the intervention to mothers with SUD undergoing treatment as usual (TAU) and to low-risk mothers. According to previous studies, we expect that (1) the quality of observed parenting behaviors in SUD mothers is higher after the intervention compared to the randomized control group receiving TAU and (2) mothers with SUD will, at pretest, show poorer parenting behaviors compared to the low-risk group.

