### Aims and hypotheses

Our primary aim is to investigate intervention effects on the quality of parenting measured through observed parenting behaviors, in mothers with SUD. We will investigate whether the intervention affects sensitive parenting and gentle but consistent discipline. We expect that, from pre-test to post-test, the quality of observed parenting in the SUD experimental group increases more or decreases less than in the SUD control group.Our secondary aim is to investigate intervention effects on parental cognitive mechanisms. We will investigate whether the intervention affects the mothers’ performances on (2a) an attentional bias reaction time paradigm aimed at measuring attentional bias to negative emotions and on (2b) a go/no-go task involving child faces displaying different emotions aimed at measuring inhibitory control in response to child emotions, respectively. Moreover, we will investigate whether the intervention affects (2c) self-perceived reflective functioning. We expect that the intervention modifies the mothers’ performances on the two tasks and self-reported reflective functioning in the SUD experimental group with respect to the SUD control group.Our tertiary aim is to investigate whether changes in parental cognitive mechanisms affect intervention effect on parenting. Specifically, we will investigate whether changes in the mothers’ (3a) attentional bias, (3b) inhibitory control, and (3c) reflective functioning account for changes observed in parenting. Specifically, we expect that improvements in the mothers’ performances on the cognitive measures will be associated to improvements in the quality of observed parenting in the SUD experimental group (Fig. 1).Our fourth objective is to explore whether the administration of the intervention has an effect on parenting stress. Specifically, we expect that, after the administration of the VIPP-SD, perceived parenting stress in the SUD experimental group decreases compared to the SUD control group.Our fifth objective is to compare the SUD experimental group and the SUD control group to the low-risk group with respect to post-test measures.

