## Methods/design

### Study design

The study is a randomized wait-list controlled trial aimed at investigating the role of parental inhibitory control, attentional disengagement, and reflective functioning in the efficacy of the VIPP-SD, an evidence-based parenting intervention, in mothers with SUD. The protocol was developed in line with the SPIRIT guidelines ([116], see Additional files 1 and 2). The project will involve a group of mothers with SUD and a group of low-risk mothers. The intervention will be randomly delivered to half of the mothers in the SUD group, through a wait-list approach. Specifically, mothers from the SUD group will be randomly assigned to one of two conditions: (1) an experimental condition (SUD experimental group), treated with the VIPP-SD, and (2) a wait-list condition (SUD control group), with TAU. Participants in both groups will be assessed pre- and post-treatment/wait-list for primary and secondary outcome measures. Participants in the SUD experimental group will be reassessed at a 2-month follow-up, to see whether outcomes measured during the post-test phase remain stable, whereas at the end of the post-test phase participants in the SUD control group will be administered the intervention.

Mothers in the low-risk group will undergo two measurements (respectively assessment 1 and assessment 2) where we will collect the same measures collected in the SUD group (quality of parenting behaviors, attentional disengagement, inhibitory control, reflective functioning, parenting stress, maternal general executive functioning, and psychopathology). The two measurements in the low-risk group are scheduled at a 3-month distance, a time frame that equals the length of the VIPP-SD, and will serve as a comparison for the pre-test and the post-test phase of the SUD experimental group. Figure 2 presents the diagram of participants’ flow through the trial.

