#### Sample size and power

The sample size for the study was calculated based on power, level of significance, and size of the treatment effect expected [124], referring to previous study reporting on RCTs addressed to mothers with SUD [86]. Power was set at the conventional level of 80%. Regarding the size of the expected treatment, recent meta-analytic work testing the effectiveness of VIPP-SD on sensitive parenting yielded a combined effect size of *d* = 0.47, indicating that the intervention significantly increases sensitive caregiving [21, 125]. For the purposes of the present study, a statistical power analysis was performed for sample size estimation (repeated measures ANOVA within-between interaction, G*Power 3.1.9.2). For our primary, secondary, and fourth aims, testing the effect of the intervention on parenting and on parental cognitive mechanisms through repeated measures analyses with *α* = .05, a statistical power (1 − *β*) = 0.80, and a medium-sized effect of *d* = 0.47, a minimum sample size of *n* = 34 is required. For our third and fifth aims, testing mediating mechanisms, the proposed sample size ensures a power >80% since the power to detect mediating effects is generally larger than it is for main effects [126]. Considering the high risk of attrition in the SUD group, we will adopt oversampling strategies when managing missing data [127] and intention-to-treat analyses [128], in order to preserve statistical power.

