#### Fifth aim

Our fifth objective is to compare the SUD experimental group and the SUD control group to the low-risk group. To do this, we will compare the post-test measurements of the experimental and control SUD groups with the two assessments in the low-risk comparison group.

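### The fifth aim compares the SUD arms with low-risk mothers, but the protocol gives it a mediation analysis and a mediation-based power claim, and its time points do not agree

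*Protocol article*

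**What the plan says.** The Aims and hypotheses section sets the fifth objective as "to compare the SUD experimental group and the SUD control group to the low-risk group with respect to post-test measures". The Fifth aim section under Measures keeps both SUD arms and the SUD post-test, but adds a second low-risk time point: "we will compare the post-test measurements of the experimental and control SUD groups with the two assessments in the low-risk comparison group". Study design says that the two low-risk assessments, three months apart, "will serve as a comparison for the pre-test and the post-test phase of the SUD experimental group".

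The Statistical analyses section groups this aim with the tertiary one: "For our tertiary and fifth aims, we will use the Montoya and Hayes approach [157] in a repeated measures design". The sentence goes on to give the purpose: "to test whether changes in cognitive mechanisms mediate the intervention effects on parenting". Its other models are tied to the primary, secondary and fourth aims, with experimental condition as the between-subjects factor. Sample size and power makes the same pairing, "For our third and fifth aims, testing mediating mechanisms", and claims power above 80% because mediating effects are said to be generally easier to detect than main effects.

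Separately, the Background states SUD v low-risk hypotheses at pre-test for parenting ("mothers with SUD will, at pretest, show poorer parenting behaviors compared to the low-risk group"), attentional bias, inhibitory control and reflective functioning. It also asks whether the intervention narrows the difference from low-risk mothers.

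**The concern.** A mediation analysis of the intervention effect estimates how much of the effect on parenting runs through change in a cognitive measure. It does not return a mean difference between mothers with SUD and low-risk mothers, who are neither randomised nor given the intervention. The pairing appears in both the power text and the analysis text, so a statistical analysis plan written from this protocol could inherit it.

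One of five stated aims depends on this, and so does the use made of 20 of the 60 mothers. With the analysis misassigned and the time points unsettled, the contrast could be chosen after the data are seen. The power statement would also lead a reader to expect a sensitivity that nothing in the document supports.

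**Working it through.** **1. Aim against analysis.** The aim asks for the difference between each SUD arm and the low-risk group. The assigned analysis asks for an indirect effect of the intervention. These are different estimands, and the second does not yield the first.

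**2. Time points side by side.**

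| Section | SUD group named | SUD time point | Low-risk time point |
|---|---|---|---|
| Aims and hypotheses | both arms | post-test | not separately stated |
| Fifth aim (Measures) | both arms | post-test | both assessments |
| Study design | experimental arm | pre-test and post-test | both assessments |

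The first two agree on the SUD side. They leave open whether the low-risk reference is assessment 2 or both assessments. Study design brings in the SUD pre-test and does not mention the control arm.

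**3. The plan's own figure.** Power above 80% for the fifth aim cannot be reproduced: no SUD v low-risk effect size, alpha or formula is given for it. The d = 0.47 in the same section is the expected intervention effect, and the minimum of 34 belongs to the primary, secondary and fourth aims.

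**4. Power as a group comparison (illustrative).** Inputs from the protocol: 40 SUD mothers allocated 1:1, so 20 per arm, and 20 low-risk mothers. Assumed: two-sided alpha 0.05 (0.05 is stated for other aims, sidedness is not) and the gap d in SD units.

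Formula: two-sample t test with df = n1 + n2 − 2 and noncentrality δ = d·√(n1·n2/(n1 + n2)). Power is the probability that the noncentral t exceeds the two-sided critical value in absolute size.

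One SUD arm v low-risk: √(400/40) = 3.162, df = 38.
- d = 0.47: δ = 1.49, power 30.5%
- d = 0.6: δ = 1.90, power 45.6%
- d = 0.8: δ = 2.53, power 69.3%
- d = 0.91: δ = 2.88, power 80.1%

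The 95% CI half-width is 2.024 × √(1/20 + 1/20) = 0.64 SD. If only the minimum of 34 SUD mothers were analysed (17 per arm), power would be 28.3% at 0.47 and 65.5% at 0.8.

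All SUD v low-risk, relevant at pre-test: √(800/60) = 3.651, df = 58.
- d = 0.47: δ = 1.72, power 39.3%
- d = 0.8: δ = 2.92, power 81.9%
- 80% power is reached at about d = 0.78

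**5. Does a post-test comparison speak to a narrowing gap?** Let E, C and L be the post-test means of the experimental, control and low-risk groups, with higher scores better. The gaps are L − E and L − C. Control gap minus experimental gap = (L − C) − (L − E) = E − C. Under randomisation the control gap estimates what the gap would have been without VIPP-SD, so this difference estimates the reduction. The low-risk mean cancels: the reduction is the randomised contrast, and the low-risk group shows how large the remaining gap is.

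**The case against.** The strongest reply is that this is a slip of numbering. The Fifth aim section plainly describes a group comparison, all three groups are to be measured twice on the same instruments, and a condensed article may leave the model to a fuller plan. Much of that stands: the planned data can answer the aim, and silence about the model would be no fault. But the article is not silent. It names a method that does not fit, in two sections, and attaches a power figure to it.

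A reader might go further in three ways that the document does not support.
- That a post-test comparison cannot show a reduction because it ignores the gap at entry. Both SUD arms are compared and they were randomised, so step 5 applies. Pre-test data would add precision but are not required.
- That the pre-test hypotheses contradict the fifth aim. They are separate statements about baseline differences, never labelled as the fifth aim, and can coexist with a post-test objective. That the article names no model for them is ordinary condensation.
- That a non-significant post-test gap would be reported as normalisation. No section plans that reading.

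It is also fair that the assumed gaps are not the trial's own, and that 0.47 as a SUD v low-risk gap is only a convenient reference value. The figures show how little a comparison of this size can detect; they do not measure the harm done by the misassigned method.

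**Conclusion.** The point holds in this form. The analysis and the power stated for the fifth aim are wrong as written, because both treat a group comparison as mediation. A narrower inconsistency in time points remains between Aims and hypotheses, Fifth aim and Study design.

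On the assumptions in step 4, power above 80% needs a gap of about 0.91 SD for one SUD arm v low-risk, or about 0.78 SD for all SUD v low-risk at pre-test. At smaller gaps the claim fails, down to about 31% for 20 v 20 at 0.47 SD. Larger true gaps are possible; the documents give no basis for choosing.

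It would be too strong to infer that the low-risk group can yield no valid test: the planned measurements allow one once the right analysis is named. The primary, secondary and fourth aims have their own models and are untouched. This should be fixed, but it does not threaten the trial's main result.

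**What to change.** - Remove the fifth aim from the mediation sentences in Sample size and power and in Statistical analyses, leaving mediation to the tertiary aim.
- Name a group comparison for the fifth aim. One option is a three-group, group-by-time linear mixed model, with a pre-test contrast of pooled SUD v low-risk (matching the Background hypotheses) and post-test or change contrasts of each SUD arm v low-risk. Separate contrasts would also serve.
- Judge any narrowing of the gap by comparing the experimental arm's gap with the randomised control arm's gap, and report confidence intervals.
- State one set of time points, and use it in Aims and hypotheses, Study design and Fifth aim.
- Withdraw the claim of power above 80% for this aim. Either call the aim exploratory or restate its power from a declared SUD v low-risk gap.

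The cost is wording only. The measurements needed are already planned for all three groups, although the Trial status section shows recruitment running to October 2023, so they should not be described as already collected.

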## Abstract

**Background:**

Maternal substance use disorder (SUD) represents a risk condition for quality of parenting and child development. The current literature highlights the need to identify interventions that effectively enhance the quality of parenting and to better understand which mechanisms are involved in the process of change. The present study protocol describes a randomized wait-list controlled trial that aims to examine (1) the efficacy of the Video-feedback Intervention to promote Positive Parenting and Sensitive Discipline (VIPP-SD) in improving the quality of parenting (i.e., sensitive parenting and sensitive discipline) in mothers with SUD, (2) whether the intervention affects parental cognitive mechanisms (i.e., attentional disengagement to infant negative emotions, inhibitory control confronted with children’s affective expression, and parental reflective functioning), and (3) whether changes in these processes act as mechanisms of change, mediating the effect of the VIPP-SD program on quality of parenting. Moreover, the study aims (4) to explore whether the VIPP-SD has an effect on parenting stress and (5) to compare mothers with SUD to low-risk mothers on the outcome measures.

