#### Wait-list group

The experimental SUD group will be administered the VIPP-SD immediately after the pre-test phase whereas, during this period, participants in the SUD control group will undergo TAU which involves individual and group psychotherapy, psychopharmacological treatment, and educational intervention. After the post-test phase, the intervention will be delivered also to the wait-list group.

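### As worded, the tertiary mediation analysis takes pre versus post as its exposure and gives randomised condition no stated place, so change shared by both arms can be reported as mediation of the VIPP-SD effect

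*Protocol article*

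**What the plan says.** The Statistical analyses section assigns models by aim. "For the primary, the secondary, and the fourth aims, we will first adopt linear mixed models for intent-to-treat analyses", followed by repeated measures models on complete cases. To estimate the intervention effect on parenting and on the cognitive mechanisms, "we will define experimental condition as between-subjects factor and time-point measurements as within-subjects factor". The tertiary and fifth aims get a different tool: "we will use the Montoya and Hayes approach [157] in a repeated measures design to test whether changes in cognitive mechanisms mediate". What is to be mediated, according to the same sentence, is the effect of VIPP-SD on parenting.

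The Abstract states the goal as mediators "mediating the effect of the VIPP-SD program on quality of parenting". Under Aims and hypotheses, the tertiary expectation is that improvements on the cognitive measures "will be associated to improvements in the quality of observed parenting in the SUD experimental group". The expectations for the primary, secondary and fourth aims in that section all name the SUD control group as comparator. The tertiary one does not.

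Under Study design, "mothers from the SUD group will be randomly assigned to one of two conditions", and "Participants in both groups will be assessed pre- and post-treatment/wait-list for primary and secondary outcome measures". Under Wait-list group, "participants in the SUD control group will undergo TAU which involves individual and group psychotherapy, psychopharmacological treatment, and educational intervention".

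**The concern.** The trial asks whether change in a mechanism carries the effect of VIPP-SD, so the exposure is randomised condition. In a two-occasion within-person mediation model the exposure is the repeated factor. Up to post-test that factor is time, which every mother in both arms experiences.

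Pre-to-post change contains more than the intervention. The mediators include two computerised tasks given twice. The children are toddlers and preschoolers assessed over roughly three months. The control arm receives active usual care. If these move a mediator in everyone, and mothers who change more on the mediator also change more on parenting, the within-person indirect effect differs from zero even when VIPP-SD does nothing. The control arm is there to subtract that shared change, and the mediation sentence does not use it. At stake is the mechanism claim, one of the paper's headline aims.

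**Working it through.** **Inputs from the protocol.** 40 SUD mothers (Recruitment), 1:1 allocation (Randomization), so 40 / 2 = 20 per arm; α = .05 (Sample size and power). The protocol states no figure for the mediation analysis that can be reproduced: it asserts power above 80% but gives no path coefficients.

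**Assumed, because the protocol does not give them.** No arm effect on mediator or parenting; a common shift δ in the mediator of 0.3 to 0.5, in SD of the change score; a correlation r between mediator change and parenting change of 0.3 to 0.5; complete data.

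**The two indirect effects.** Write ΔM and ΔY for pre-to-post change in mediator and parenting.

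- Within-person: a = mean(ΔM); b = slope of ΔY on ΔM; indirect effect a × b.
- Arm-based: a = mean(ΔM, experimental) − mean(ΔM, control); b = slope of ΔY on ΔM adjusted for arm; indirect effect a × b.

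Under the assumed null, with change scores at unit SD so that b = r:

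- Within-person: a × b = δ × r, which runs from 0.3 × 0.3 = 0.09 to 0.5 × 0.5 = 0.25.
- Arm-based: a = δ − δ = 0, so a × b = 0.

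The true mediated effect of VIPP-SD in this scenario is 0.

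**How often mediation is declared.** Simulation, with mediation declared when both paths have p < 0.05:

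| δ | r | 20 experimental mothers | 40 pooled |
|---|---|---|---|
| 0.3 | 0.3 | 5% | 20% |
| 0.5 | 0.3 | 14% | 42% |
| 0.3 | 0.5 | 15% | 42% |
| 0.5 | 0.5 | 34% | 80% |

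The arm-based model with 40 mothers stays at about 2 to 4% in every setting. With δ = 0 the within-person test shows no excess.

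**Rough check by hand.** The two path tests are close to independent, so the joint rate is about the product of their separate rates. The test of a has noncentrality δ√n.

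- δ = r = 0.5, n = 20: 0.5 × √20 = 2.24, giving 0.57 for path a. Path b at r = 0.5 gives about 0.64. Product: 0.57 × 0.64 = 0.36.
- δ = r = 0.5, n = 40: 0.5 × √40 = 3.16, giving 0.87. Path b gives about 0.92. Product: 0.87 × 0.92 = 0.80.
- δ = r = 0.3, n = 20: about 0.25 × 0.25 = 0.06.
- Arm-based: path a is null, so its rate is 0.05 and the product cannot exceed about 5%.

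**Second method.** A percentile bootstrap of the indirect effect (1,000 trials, 500 resamples, pre-post correlation 0.5), with the within-person model also adjusting for the centred mediator sum, agrees. At that correlation the SD of change is √(2 × (1 − 0.5)) = 1, so the scales match. False mediation with 20 mothers was 6 to 16% at δ = 0.3 and 16 to 35% at δ = 0.5. Pooled, it was 21 to 44% and 45 to 80%. The arm-based version gave about 2 to 6%. With no shift all three stayed at about 2 to 7%.

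**The case against.** The strongest reply is that the protocol nowhere says arm is left out. The mediation sentence ends by referring to intervention effects, and the sentence before it defines condition as a between-subjects factor without expressly limiting this to some aims. The same mediation sentence also covers the fifth aim, a comparison between groups, which sits badly with a single-group analysis. How arm enters could be detail left to a fuller document. This stands in part: exclusion of arm is an inference. But the section names a method for this aim, describes it as repeated measures, and pairs it with a hypothesis set inside the experimental group. That is a mismatch between method and question, not mere silence.

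Second, aims 1 and 2 test arm effects on parenting and on each mediator, and those results would be reported alongside. In a re-run of the null scenario (pre-post correlation 0.5 assumed), a significant within-person mediation result together with significant arm differences in both mediator and parenting change occurred in under 1% of trials. The low-risk group's two assessments, three months apart, also give some information on retest and maturation. This guards the interpretation. It does not make the mediation test valid for the claim attached to it.

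Third, the high rates depend on assumptions. The attention index is a difference between two reaction-time means, so general speeding partly cancels, and reflective functioning is a questionnaire, not a practised task. A uniform 0.5 SD gain is therefore not established. This is correct, and it is why a range is given. The pooled figures also need all 40 mothers in one within-person model, whereas the stated hypothesis points to the experimental group.

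**Conclusion.** The point holds in limited form. As worded, the tertiary analysis takes pre versus post as the exposure, while the Abstract and the Statistical analyses section claim mediation of the intervention effect. Under no arm effect, a common shift of 0.3 to 0.5 SD of change and a correlation of changes of 0.3 to 0.5, false mediation is about 5 to 34% in the 20 experimental mothers and 20 to 80% in 40 pooled, against about 2 to 4% for an arm-based model. The excess vanishes if nothing shifts over time, and at the low end with 20 mothers there is essentially none.

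A reader might infer that the plan expressly drops randomised condition, or that one false mediation claim in three is to be expected. Neither is supported: the first is not stated, and the second is the top of an assumed range for the experimental arm. Nor does this touch the primary inference, which uses condition by time. It should be corrected, at the weight of a tertiary aim.

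**What to change.** State that randomised condition is the exposure in the tertiary mediation analysis, and that all randomised SUD mothers are included. Then specify:

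- Path a: the effect of arm on the post-test mediator, adjusted for the baseline mediator.
- Path b: the effect of the post-test mediator on post-test parenting, adjusted for arm, baseline mediator and baseline parenting.
- The executive-function and psychopathology controls already planned under Control variables are kept.
- A bootstrap interval is reported for the indirect effect.

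The exact covariate set is partly a matter of choice; arm as the exposure is not. Align the tertiary hypothesis under Aims and hypotheses with this contrast. Keep the within-person analysis as descriptive only, and note that mediator and outcome are measured at the same visit, so their order in time is not established.

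The cost is a change of wording, using data already planned in both arms. The small downside is a wider interval for the indirect effect.
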